**Communication**				
	Physician	Need for physician communication about mutation Investigator developed 10 items, 7-point Likert scale	√	
	Family	Mutuality & Interpersonal Sensitivity [86] 15 items, 7-point Likert scale	√	√
		Family Support in Illness [73,87] 10 items, 7-point Likert scale	√	√
		Communication with children & relatives about mutation (previously used) [29] 17 items (multiple choice)	√	
**Genetic services**				
	Genetic services	Barriers & facilitators (previously used) [29,88] 11 items, 7-point Likert scale & 22 items (multiple choice)	√	√
	Genetic testing	Had genetic testing (yes/no) Self-reported	√	√
	Referral	Source & involvement (previously used) [29] 16 items (multiple choice)	√	
	Quality of Life	SF-12 [89] Physical component & Mental component	√	√

### Data Analyses

Selection bias will be minimized by random selection of mutation-harboring families in each clinical site from three linguistic regions of Switzerland. Stratification will ensure selection of an equal proportion of index cases from clinical sites that offer genetic services for both syndromes. The study will try to recruit all index cases from clinical sites including fewer than 100 mutation-harboring HBOC/LS families to ensure a representative sample.

All statistical analyses will be conducted in licensed software packages, including Microsoft Excel, SPSS (IBM), and R. For all statistical tests, significance will be set at two-sided alpha=.05. Data values will be examined for legality (within appropriate range) using histograms and box plots and corrected when possible. Descriptive analyses will include calculating means, standard deviations, frequencies, and percentages of variables and participant descriptors. Bivariate analyses (Pearson correlations, chi-square test for differences in proportions, and *t* test for differences in means) will assess associations between demographics and clinical characteristics. Regression analyses will incorporate generalized estimating equations for pairing index cases with their relatives and explore to what extent predictors are in direct, mediating, or moderating relationship to an outcome.

The following comparisons will take place: between index cases and relatives, between HBOC and LS, between men and women, cancer patients versus cancer-free individuals, participants with children versus those with no children, between different age groups and different cancer diagnoses. Data from participants who withdraw will be kept in the study to ensure the internal validity of the study. Missing data from multi-item scales will be addressed with multiple imputations using R software if they exceed 5% of observations and if they are less than 25% for each specific scale. Scale reliability will be assessed with Cronbach alpha and principle component analyses. Deviations from the planned analyses are not foreseen. The study statistician will review and approve any deviations from the original statistical plan if necessary.

Narrative data from focus groups will be recorded and transcribed verbatim to allow data management and content examination. Thematic analyses to inductively classify data in concepts and categories, as these emerge through an interpretive process, will be carried out under the guidance of the qualitative methodologist [90]. Focus group participants will be shown a prototype of a family-based intervention as a PowerPoint presentation. Then they will be asked if they like the intervention, if they find it useful, and how it can be improved. Acceptability of the intervention will be assessed with a short survey using 7-point Likert-type items (1=Low to 7=High) asking overall satisfaction with the content, format and appearance of the program, and whether it can help with family communication, coping, and decision making. The survey assesses six acceptability items: ease of use, clarity, appropriate length, appropriate level of detail, able to hold interest, and satisfaction.

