## Methods

### Design

CASCADE is a longitudinal study using surveys and focus groups, designed to elicit factors that enhance cascade genetic testing for HBOC and LS in Switzerland. The CASCADE study will contact known mutation carriers for HBOC and LS and systematically identify and contact their relatives to determine if they have had genetic testing, if they also carry the pathogenic variant, and how they manage their risk for hereditary cancer. Repeated observations are the optimal way for assessing these outcomes. The study will also use focus groups to examine the acceptability of a family communication, coping, and decision support intervention (Phase I). Table 1 presents a detailed description of assessments conducted for the study. The study protocol has been approved by the local ethics committee, while approval from ethics committees in other cantons is underway. The study will be carried out according to principles described in the Declaration of Helsinki and applicable Swiss laws and Swiss regulatory authority requirements.

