**Figure 1 figure1:**
[figure not shown]
Expected recruitment of index cases.

Estimates of sample size are based on the PI’s experience, consultations with medical directors of clinical sites, and assuming average prevalence rates of 5% for hereditary breast cancer and 2-5% for hereditary colorectal cancer (the two most common manifestations of HBOC and LS), respectively. Assuming that is feasible to recruit 10% of mutation carriers from each participating clinic, 300 index cases will be targeted for inclusion within 12 months. It is expected that around 70% of approached index cases will accept participation, meaning that 495 index cases need to be approached to reach 305. It is estimated that from each index case we will identify 2.5 relatives. Assuming a response rate of 50% among relatives, we expect to recruit approximately 381 relatives. Figure 1 presents the CONSORT [68] diagram for recruitment of expected index cases and relatives.

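### The simple bivariate tests are not limited to one person per family, so on the pooled sample their 5% level fails for factors shared by a family and for index cases versus relatives

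*Protocol article*

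**What the plan says.** All of this is in the protocol article. Under Data Analyses, one rule covers every test: "For all statistical tests, significance will be set at two-sided alpha=.05". The simple tests are then named: "Bivariate analyses (Pearson correlations, chi-square test for differences in proportions", followed by the t test for means. Their stated job is that they "will assess associations between demographics and clinical characteristics". Nothing limits them to index cases or to one member per family, and no correction for clustering is attached.

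Family correlation appears only in the next sentence, for the models: "Regression analyses will incorporate generalized estimating equations for pairing index cases with their relatives". The following paragraph opens the list of contrasts: "The following comparisons will take place: between index cases and relatives, between HBOC and LS, between men and women", and continues with cancer status, children, age group and diagnosis. No test or model is assigned to any of them.

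Under Sample and Sample Size, the recruitment target is "495 index cases need to be approached to reach 305". That section also expects 2.5 relatives per index case, half of whom respond, giving about 381 relatives. Under Data Collection and Data Management, each participant gets a code that ties them to their family, so a cluster identifier exists.

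**The concern.** Pearson, chi-square and t tests assume that each observation is independent of the others. Here the participants come in families. Table 2 shows that most scales are completed by both index cases and relatives, and some of them measure family support and mutuality directly, so positive correlation within families is plausible.

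The direction of the error depends on the factor. Syndrome is the same for every member of a family, so relatives add less information than their number suggests and an independence test rejects too often. Index case versus relative is a contrast inside the family. There the shared family component partly cancels, and an independence test rejects too rarely. These are the first two contrasts on the list. At stake are false positives for family-level factors and lost power for index cases against relatives.

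**Working it through.** **Inputs from the article.** Two-sided alpha 0.05; 305 index cases, one per family; 2.5 relatives per index case; 50% response among relatives. **Assumption.** The within-family correlation (ICC) is not given; the range 0.05 to 0.5 is used.

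**Reproducing the plan's figure.** 305 × 2.5 × 0.50 = 381.25, so 381 relatives reproduces. Mean family size is (305 + 381)/305 = 2.25. The article also gives 300 as the index-case target; the mean is the same, because 1 + 2.5 × 0.50 = 2.25.

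**Factor constant within a family (HBOC versus LS).** Design effect DEFF = 1 + (m − 1) × ICC, where m is the size-weighted mean family size. True type I error = 2 × [1 − Φ(1.96/√DEFF)]. With equal families m = 2.249. With a Poisson number of relatives (mean 1.249), m = (2.249² + 1.249)/2.249 = 2.805. The t test was also simulated (4,000 data sets, Poisson relatives, each family assigned to either syndrome with probability one half).

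| ICC | DEFF, equal / Poisson | Type I error, equal / Poisson | Simulated t test |
|---|---|---|---|
| 0.05 | 1.062 / 1.090 | 5.7% / 6.1% | not run |
| 0.1 | 1.125 / 1.180 | 6.5% / 7.1% | 6.7% |
| 0.3 | 1.375 / 1.541 | 9.5% / 11.4% | 11.1% |
| 0.5 | 1.625 / 1.902 | 12.4% / 15.5% | 15.9% |

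A third family structure (two or three relatives invited, 50% response, 30% LS families) has m = 2.56. It simulates at 7%, 11% and 15% for ICC 0.1, 0.3 and 0.5.

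**Contrast inside the family (index cases versus relatives).** True variance = 1/305 + (1/381) × [1 + (r − 1) × ICC] − 2 × ICC/305, divided by the independence variance 1/305 + 1/381. Here r is the size-weighted number of relatives: 1.249 if equal, 2.249 if Poisson. Example for Poisson at ICC 0.3: (0.003279 + 0.002625 × 1.375 − 0.001967)/0.005903 = 0.833. The error rate follows as above, with this ratio in place of DEFF.

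| ICC | Variance ratio, equal / Poisson | Type I error, equal / Poisson | Simulated t test |
|---|---|---|---|
| 0.1 | 0.900 / 0.944 | 3.9% / 4.4% | 4.7% |
| 0.3 | 0.700 / 0.833 | 1.9% / 3.2% | 3.0% |
| 0.5 | 0.500 / 0.722 | 0.6% / 2.1% | 2.2% |

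The third family structure simulates at 4%, 2.5% and 1%.

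**Chi-square.** With a 40% outcome and latent correlation 0.1, 0.3 and 0.5, simulated error is 6.1%, 9.3% and 11.3% for HBOC versus LS, and 4.5%, 3.6% and 3.0% for index cases versus relatives.

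**Factor varying at random within families (sex).** The simulated t test stays at 5.1-5.2% throughout.

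**After the fix.** GEE with family as the cluster and exchangeable correlation (500 runs, simulation error about 1 point) gives 5.2%, 4.0% and 4.8% for HBOC versus LS, and 4.8%, 4.4% and 6.2% for index cases versus relatives. That is nominal within simulation error.

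No figure was computed for the Pearson correlation. Its error depends on how strongly both variables correlate within families.

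**The case against.** The strongest reply is that the simple tests have a narrow stated job. A reader might infer that they will produce the listed comparisons, but the text does not say so; the list stands in its own paragraph with no test attached, after the GEE regressions. This stands, and it limits the point. It does not remove it. Syndrome is itself a clinical characteristic, so the narrow job already includes a factor fixed within families. For index cases versus relatives, the gap is that no method is named.

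A reader might also infer that the GEE will be built on index-relative pairs, counting an index case once per relative. Nothing in the text describes that. With family codes in place, family as the cluster is the natural reading, and it is sound.

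Nor can the missing model for yearly data be held against the plan, although the design section says "Repeated observations are the optimal way for assessing these outcomes". The article is condensed and the full plan is not shown. Yearly contact is optional, and one completed survey is the minimum for taking part.

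Language should not be counted as a family-level factor, because preference is recorded per person. Finally, the study is largely descriptive and exploratory, with no stated power target or confirmatory hypothesis, which lowers the stakes.

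**Conclusion.** The point holds in a limited form. As written, independence tests at two-sided 5% may be run on a sample averaging 2.25 related people per family, and no method is fixed for the listed contrasts. On the pooled sample, type I error would be about 7%, 11% and 15% for HBOC versus LS, and about 4-5%, 2-3% and 1-2% for index cases versus relatives, at ICC 0.1, 0.3 and 0.5.

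These sizes rest on an assumed ICC and, to a lesser degree, on the assumed spread of family sizes. At ICC 0.1 or below the distortion is small. It would be wrong to conclude that p-values fail throughout the plan: regressions with family-clustered GEE are valid, factors such as sex are little affected, and scales given only to index cases (for example decisional regret and referral) have one respondent per family. This is a worthwhile correction of wording, not a defect that invalidates the study.

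**What to change.** State in the analysis section that every test or comparison pooling more than one person per family uses GEE, or a mixed model, with family as the cluster, one record per person and robust standard errors. A logit link takes the place of the chi-square test and an identity link the place of the t test. Assign this method explicitly to the listed comparisons. Keep plain Pearson, chi-square and t tests for analyses with one person per family, such as index cases only.

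The cost is a little more analysis code, and p-values for family-level factors become less favourable. Recruitment and data collection do not change, since the family codes already exist.

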## Results

This study is currently recruiting participants.

## Discussion

### Principal Considerations

Cancer predisposition cascade genetic screening combines personalized medicine and public health. Once a mutation carrier for HBOC or Lynch syndrome is identified, evidence-based interventions are available that can reduce the risk of adverse health outcomes in entire cohorts of relatives [91]. This approach is cost-effective for Tier 1 genetic conditions, leading to reduced medical and insurance coverage costs (eg, treatment and hospitalization expenses) [92-94]. Cascade screening for FH applied in the Netherlands identified thousands of mutation carriers for the disorder and has been subsidized by the Dutch government since 2015 [95,96]. Similar programs for FH have also been implemented in Scotland and Wales [97,98].

Availability of genetic testing created an increasing demand for coordination of health care services and risk communication among index cases and relatives. Knowledge of hereditary risk can serve as an information tool to reduce cancer morbidity and mortality. This necessitates the establishment of family-based registries that systematically record genetic information. Currently, this information is fragmented and dispersed across Swiss clinical sites. The establishment of high-risk clinics would allow synergistic approaches in cancer surveillance and medical care offered to these families. Effective data sharing and dissemination across disciplines is mandatory for increasing the impact of genetic screening, ensure resource allocation, and facilitate health care policy and decision making.

### Conclusion

CASCADE study will promote multidisciplinary research in public health genetics at the cutting edge of medicine with strong translational application. This has significant potential to enhance the development of high-quality comprehensive support systems to improve use of cancer genetic services and facilitate patient involvement in health care decisions. The long-term outcome of this program is the development and implementation of new models for systematic surveillance and detection of individuals at risk for hereditary cancer in Switzerland. Immediate outcomes are the assessment of current use of cancer genetic services and evaluation of the public health impact of HBOC and LS. The CASCADE study will document the needs of mutation-harboring families, including barriers and facilitators to accessing cancer genetic services, and will promote use of family history for genetic risk assessment. The study will also provide information for the acceptability of an intervention that will potentially increase genetic literacy, expand understanding of health care technologies, and reduce HBOC- and LS-related morbidity and mortality in Switzerland.

## Abbreviations

BRCA1: breast cancer 1
BRCA2: breast cancer 2
CTU: Clinical Trial Unit
FH: familial hypercholesterolemia
HBOC: hereditary breast/ovarian cancer syndrome
HFTA: Federal Act on Human Genetic Testing
LS: Lynch syndrome
MMR: mismatch repair
MSI-H: microsatellite instability
